#### Adverse events

All participants will be requested to report adverse events (AEs), i.e., any occurrence or worsening of an undesirable sign, symptom, or disease, whether or not related to acupuncture treatment. Acupuncturists will record AEs in detail including date, type, severity, measures taken by researchers, and causal relationship with the treatment. Common acupuncture-related AEs include intolerable needling pain, hematoma, and local infection.

### Statistical considerations

#### Sample size

The results of our previous study on acupuncture for DOR [22] showed that the increase in mean AFC from baseline to week 12 was 2.25 in acupuncture group and 0.30 in the wait list control. Based on these results, we assumed an increase of 0.8 in AFC for sham acupuncture after 12-week treatment. A sample size of 50 participants per group will be needed to provide 90% power and a two-sided significance level of 5%, assuming a standard deviation of 2.22. Allowing for a 20% dropout rate, 120 participants will be recruited with 60 participants per group.

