## Study design and methods

### Study design

This is a prospective, single-center, randomized, sham-controlled trial. Participants will be assigned to receive acupuncture or sham acupuncture in a 1:1 ratio. This study is in accordance with the principles of the Declaration of Helsinki and has been approved by the ethics committee of the Institute of Acupuncture and Moxibustion, China Academy of Chinese Medical Sciences (CACMS) (approval number: SC2017-12-22-1-1). Written informed consent will be obtained from each participant before enrolment.

Total observation period will be 32 weeks, including an 8-week screening period (weeks − 8–0), a 12-week intervention period (weeks 0–12), and a 12-week follow-up period (weeks 13–24). Assessments will be conducted at baseline, week 12, and week 24. Flowchart and study design schedule are presented in Fig. 1 and Table 1, respectively.

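### Sixty per group does not keep 50 per group after 20% dropout: 48 remain, and 50 would need 63 (126 in total); the effect on power is about one percentage point

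*Protocol article*

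**What the plan says.** The Sample size section builds the number in two steps.

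- **Base size.** In the earlier study the mean AFC increase "was 2.25 in acupuncture group and 0.30 in the wait list control". For the present control, "we assumed an increase of 0.8 in AFC for sham acupuncture after 12-week treatment". The calculation is made "assuming a standard deviation of 2.22", at a two-sided 5% level, and concludes: "A sample size of 50 participants per group will be needed to provide 90% power".
- **Dropout.** "Allowing for a 20% dropout rate, 120 participants will be recruited with 60 participants per group".

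Allocation is equal (Study design: "Participants will be assigned to receive acupuncture or sham acupuncture in a 1:1 ratio"). The Statistical analysis section names the independent t test or a non-parametric test for between-group comparisons of continuous data. It analyses everyone randomised and imputes missing data by multiple imputation.

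**The concern.** A dropout rate is ordinarily a share of those enrolled. Read that way, three figures in the section cannot all be true: 50 per group needed, 20% dropout, and 60 per group recruited. Inflating for a dropout rate d means dividing by (1 − d). Multiplying by (1 + d) gives a smaller number, and the number retained then falls short of the target.

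What is at stake is the accuracy of the power statement, which readers will use to judge a null result. The dropout allowance also matters in this design. The section on concomitant treatments lets participants leave for an IVF cycle after the first 4 weeks of treatment, and pregnancy ends the intervention, while the primary outcome is read at week 12.

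**Working it through.** **Inputs (all from Sample size, except allocation from Study design).** Change with acupuncture 2.25; assumed change with sham 0.8; SD 2.22; two-sided 5%; power 90%; 50 per group required; dropout 20%; 60 per group recruited; 1:1 allocation.

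**1. Reproduce the base size.**

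Difference δ = 2.25 − 0.8 = 1.45.

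n per group = 2 × (1.960 + 1.2816)² × 2.22² / 1.45² = 49.26, rounded up to **50**. This matches the article, so the problem lies in the dropout step alone.

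**2. Apply the stated dropout to the stated recruitment.**

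60 × (1 − 0.20) = **48** per group, 96 in total. This is 2 per group below the stated requirement.

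**3. Inflate correctly.**

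50 / (1 − 0.20) = 62.5, rounded up to **63** per group, **126** in total. (Rounding only the total gives 100/0.80 = 125.) The plan is 6 short of 126, or about 5%.

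**4. Where 60 could come from.**

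50 × (1 + 0.20) = 60 exactly. The formula is inferred from this match.

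**5. Dropout that 60 per group does cover.**

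1 − 50/60 = **16.7%**, i.e. 10 of 60.

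**6. Power at the number retained.**

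Normal approximation: power = Φ(δ / (SD × √(2/n)) − 1.960).

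- n = 50: 1.45 / (2.22 × √(2/50)) = 3.266; Φ(1.306) = 90.4%.
- n = 48: 1.45 / (2.22 × √(2/48)) = 3.200; Φ(1.240) = 89.2%.

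The noncentral t distribution with 2n − 2 degrees of freedom gives the t test column.

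| Per group with data | Normal approximation | t test |
|---|---|---|
| 48 (60 less 20%) | 89.2% | 88.6% |
| 50 (stated requirement) | 90.4% | 89.9% |
| 51 | 91.0% | 90.4% |
| 60 (no loss) | 94.7% | 94.4% |
| 63 (no loss) | 95.6% | 95.3% |

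Moving from 50 to 48 costs 1.2 points (normal) or 1.3 points (t). Against the stated 90%, the shortfall is 0.8 points (normal) or 1.4 points (t). Of the 1.4, about 0.1 is already present at 50 per group and has nothing to do with dropout.

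**7. The same loss as a detectable difference.**

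At 48 per group and 90% power (normal): (1.960 + 1.2816) × 2.22 × √(2/48) = 1.47 follicles, against the assumed 1.45.

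**The case against.** **The loss is negligible beside the other uncertainty in the plan.** The sham increase of 0.8 is an assumption. At 50 per group, moving it to 0.7 or 0.9 moves t-test power to 93.3% or 85.3%, far more than the dropout step does. This stands, and it limits the weight of the point. It does not make the sentence correct.

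**The authors may have meant 20% added to the required number.** The article prints no formula, so a loose use of words is possible, and one cannot state as fact that the plan multiplied by 1.2. But the sentence speaks of a dropout rate, and under the usual meaning of that term the figures do not agree. If the looser meaning was intended, the wording still needs changing.

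**Forty-eight is a complete-case count.** The plan analyses all randomised participants with multiple imputation, and the data management section has the assessor pursue outcome data from those who discontinue. Stopping treatment therefore need not mean a missing AFC. This stands in part: 48 applies if every dropout lacks the week-12 AFC, and fewer missing values would mean higher power. However, imputation does not by itself restore lost information. AFC also needs a transvaginal ultrasound, so contact by telephone or WeChat cannot supply it. The article itself treats dropout as lost sample size, or it would not have raised 50 to 60.

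**A stronger reading is tempting.** A reader might infer that 120 participants leave the trial materially underpowered, or that more must be enrolled. The article's own figures do not support this: they put power at about 89% even when all 20% are lost to the primary outcome.

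**Conclusion.** The inconsistency is real and can be checked from the Sample size section alone. At 20% dropout, 60 per group leave 48, not the 50 said to be needed; 63 per group (126 in total) would be required to keep 50. The effect is small: power of about 89% (89.2% normal, 88.6% t) against a stated 90%. The finding is a wrong stated figure, and the design itself is not put in doubt.

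It rests on three assumptions: that the dropout rate is a share of those randomised, that loss is equal in both groups, and, for the power figure, that every dropout lacks the week-12 AFC and imputation recovers nothing. The difference of 1.45 and the SD of 2.22 are taken as the article gives them.

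**What to change.** Keep 120 and replace the dropout sentence with one that is true of 60 per group. Either of these will do:

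- *Sixty participants per group (120 in total) will be recruited; this allows for up to 16.7% dropout while retaining 50 per group (about 90% power).*
- *Sixty participants per group (120 in total) will be recruited; with 20% dropout this gives about 89% power.*

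The second keeps the stated dropout rate and is preferable if 20% is still the expected figure. The cost is one sentence and a slightly less favourable claim. No extra enrolment and no change to the analysis are needed. The article reports that recruitment was still open, so the wording can be corrected before results are reported.

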#### Statistical analysis

SPSS version 20.0 (SPSS Inc., Chicago, USA) will be used for statistical analysis. According to the intention-to-treat (ITT) principle, statistical analysis will be conducted on all randomized subjects. Missing data will be imputed using multiple imputation method. Continuous data will be presented with mean and standard deviation, or median and interquartile range, while categorical data will be presented with number and percentage. For comparison with the baseline, a paired t-test or non-parametric test will be used for continuous data, and nonparametric test for categorical data. Comparisons between groups will be analyzed using the independent *t* test or non-parametric test for continuous data, chi-square test or Fisher exact test for categorical data, and nonparametric test for ranked data. All statistical tests will be two-sided, and *p* < 0.05 will be considered statistically significant.

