### Measurements

#### Outcome measures

The primary outcome is the change of AFC from baseline to week 12. The differences between groups will be assessed. AFC is the number of visible ovarian follicles with a mean diameter of 2–10 mm observed during transvaginal ultrasound performed on menstrual cycle days 2–5. The number of antral follicles correlates with quantity of remaining follicles and with the ovarian response during COS. A low AFC is associated with poor response to ovarian stimulation during IVF.

Secondary outcomes are listed as follows.

(1) The mean change from the baseline in serum basal FSH, LH, and E2 will be compared between groups at week 12 and week 24.

Basal serum levels of FSH, LH, and E2 are measured on days 2–4 of the menstrual cycle. Basal FSH is commonly used to assess ovarian reserve, and high values greater than 10 IU/L are related with DOR and poor response to ovarian stimulation. An elevated basal estradiol level (greater than 50 pg/ml) in the early follicular phase indicates reproductive aging and hastened oocyte development.

(2) The mean change from baseline in serum AMH will be compared between groups at week 12 and week 24.

AMH is produced by the granulosa cells of primary, preantral, and antral follicles of 2–6 mm in diameter. It is a good predictor of oocyte quantity. A decrease of AMH indicates oocyte depletion. Since the level of AMH is fairly stable within and between menstrual cycles, it can be measured on any day of the cycle.

(3) The mean change from baseline in AFC at week 24 will be compared between groups.

(4) Change in the length of menstrual cycle at weeks 12 and 24. The length of menstrual cycle is divided into 3 categories: normal, antedated, or delayed menorrhea. The proportion of each category will be compared between groups at weeks 12 and 24.

(5) The mean change from baseline in the score of Self-Rating Anxiety Scale (SAS) will be compared between groups at weeks 12 and 24.

SAS is a self-rating scale for measuring the presence and severity of anxiety [20]. It consists of 20 items with 4 possible responses: (1) never, (2) rarely/sometimes, (3) frequently, and (4) always. The standard score is the integer part of the raw score (the sum of the 20 items) multiplied by 1.25. A higher score denotes more serious anxiety symptoms. In this trial, we will use a validated Chinese version of SAS [21].

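### Multiple imputation is paired with rank, chi-square and Fisher tests that do not pool directly by Rubin's rules; this affects cycle category and the non-parametric branch, not the t tests

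*Protocol article*

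**What the plan says.** All statements are in the protocol article.

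- Analysis set (Statistical analysis): "statistical analysis will be conducted on all randomized subjects".
- Missing data (same section): "Missing data will be imputed using multiple imputation method".
- Between-group tests (same section): the independent t test is named first, and the sentence continues "test or non-parametric test for continuous data, chi-square test or Fisher exact test for categorical data, and nonparametric test for ranked data".
- Comparisons with baseline (same section): "a paired t-test or non-parametric test will be used for continuous data, and nonparametric test for categorical data".
- Primary outcome (Outcome measures): "The primary outcome is the change of AFC from baseline to week 12". This is continuous, so it falls under the t test or its non-parametric alternative.
- Cycle outcome (Outcome measures): "The length of menstrual cycle is divided into 3 categories: normal, antedated, or delayed menorrhea". The proportions in each category are compared between groups at weeks 12 and 24.

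The Sample size section works from mean AFC changes and a standard deviation of 2.22, and allows for 20% dropout. The section on concomitant treatments lets women leave for an IVF cycle once the first 4 weeks of treatment are complete, so appreciable missing data are foreseen.

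**The concern.** Multiple imputation produces several completed data sets. Rubin's rules combine them through a treatment estimate and its standard error from each. The spread of the estimates across the sets carries the uncertainty due to the missing values. A rank test or a Fisher test, as usually run, returns a p value. A chi-square test returns a statistic on, here, 2 degrees of freedom. None of these is the pair that Rubin's rules need.

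The article therefore states two choices that do not fit together without a further step. For cycle category there is no other between-group test to turn to. For AFC, FSH, LH, E2, AMH and the anxiety score (SAS), the question arises if the non-parametric alternative is chosen. An analyst reaching that point could test one imputed set, stack the sets, or summarise the p values. Each treats imputed values, wholly or partly, as if they had been observed, and the choice could be made after the data are seen.

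**Working it through.** **1. Which tests pool directly**

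| Outcome | Named between-group test | Estimate and standard error from the usual output? |
|---|---|---|
| AFC, FSH, LH, E2, AMH, SAS | independent t test | yes, mean difference |
| the same | non-parametric alternative | no |
| cycle category (2 × 3 table) | chi-square or Fisher | no |

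The comparisons with baseline divide in the same way: the paired t test pools directly and the non-parametric tests do not.

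**2. The plan's own figure**

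The sample size rests on a difference in means: 2.25 − 0.8 = 1.45, SD 2.22, two-sided 5%, 90% power.

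n per arm = 2 × [2.22 × (1.960 + 1.282) / 1.45]² = 49.26, rounded up to 50.

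This agrees with the 50 stated and shows that the trial was sized on the scale of the t test.

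**3. Why the shortcuts inflate error**

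Inputs: 60 women per arm and 20% missing (the dropout allowance), so 48 observed and 12 imputed. Assumptions: missing completely at random, proper imputation within arm, m = 5.

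The mean of one completed arm is the observed mean plus 12/60 = 0.2 times the imputation noise. That noise has variance σ²/48 + σ²/12 = 0.10417σ².

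- Single set: true variance = σ²(1/48 + 0.2² × 0.10417) = 0.0250σ². The test assumes σ²/60 = 0.01667σ². Ratio 1.5.
- Five sets stacked: true variance = σ²(1/48 + 0.2² × 0.10417/5) = 0.02167σ². The test assumes σ²/300 = 0.00333σ². Ratio 6.5.

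Approximate rejection rates at a nominal 5%:

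- Two-sided comparison of means, which the rank test follows closely here. Single: 2[1 − Φ(1.96/√1.5)] = 2[1 − Φ(1.600)] = 11.0%. Stacked: 2[1 − Φ(1.96/√6.5)] = 2[1 − Φ(0.769)] = 44.2%.
- Chi-square on 2 df, critical value 5.991. Single: exp[−5.991/(2 × 1.5)] = 13.6%. Stacked: exp[−5.991/(2 × 6.5)] = 63.1%.

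**4. Simulation**

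Settings: 4,000 null trials under the assumptions above. Normal imputation was used for the continuous outcome, and null category proportions of 0.50/0.25/0.25 (assumed) for the 2 × 3 table.

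| Procedure | Mann-Whitney | Chi-square, 2 × 3 |
|---|---|---|
| one imputed set | 11.1% | 13.1% |
| median of 5 p values | 8.1% | 10.3% |
| 5 sets stacked | 44.2% | 62.6% |

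Repeat runs agreed to within about one percentage point. The simulation standard error at 11% is √(0.11 × 0.89/4,000) = 0.5 points. The mean difference pooled by Rubin's rules rejected in 4.6% and 4.9% of trials in two runs.

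**5. Can the other tests be pooled validly?**

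Yes, with a rule that the article does not name. With 2,000 null trials and 20 imputations:

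- pooled t test: 4.95%;
- Mann-Whitney probability with its standard error, pooled by Rubin's rules: 5.0%;
- chi-square statistics combined by the D2 rule: 6.65%. A separate run of D2 gave 5.4%, and a run with m = 5 gave 4.7%, so it is near nominal but not exact.

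At the protocol's difference of 1.45 and SD 2.22, the pooled t test rejected in 86.7% and the pooled rank comparison in 86.3%. No comparable rule was applied to Fisher's p value.

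**The case against.** A reader might infer that the imputed analysis cannot be carried out at all. The document does not support that. The t tests are named first, pool directly and match the basis of the sample size, so the primary analysis is feasible by that route. Chi-square statistics can be combined by D2, and a rank comparison can be pooled through the Mann-Whitney probability. Fisher's test is offered only as an alternative to chi-square. This part of the objection stands.

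A reader might also take the inflated rates as the error rate of this plan. They are not. The article never proposes a single imputed set, stacking or a median p value. The rates show what is at stake if the gap is filled badly, not what the plan prescribes.

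Finally, an article commonly leaves the imputation model, the number of imputations and the pooling rule to the statistical analysis plan. That is fair, and their absence is not the point made here. The point is narrower: the tests the article does fix for cycle category, "chi-square test or Fisher exact test for categorical data, and nonparametric test for ranked data", do not supply what multiple imputation ordinarily pools. An analysis plan could solve this, but it would have to add to those tests or replace them.

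**Conclusion.** The point holds in limited form. Multiple imputation of all randomised women is combined with tests to which Rubin's rules do not apply directly. Cycle category at weeks 12 and 24 is certainly affected; any continuous outcome, AFC included, is affected only if the non-parametric branch is used. The primary analysis by t test is sound in this respect.

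The size is conditional. With ad hoc shortcuts, type I error would be about 8–14% for a single set or a median p value and above 40% for stacked sets. With a valid combining rule it stays close to 5%. These figures rest on 20% missing completely at random in each arm, m = 5, normal continuous data and assumed category proportions. Less missing data would shrink the inflation. This is a worthwhile clarification, chiefly for secondary outcomes.

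**What to change.** For each outcome analysed on imputed data, name one baseline-adjusted model and pool its treatment estimate and standard error by Rubin's rules:

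- AFC and SAS: linear model.
- FSH, LH, E2 and AMH: linear model, on the log scale if skewed, with that choice settled before allocation is revealed.
- Cycle category: multinomial logistic model for the three categories or, if some are sparse, a logistic model of normal versus not normal, with the choice stated in advance. A plain logistic model without a stated dichotomy would not suit a three-category outcome.

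Keep the rank, chi-square and Fisher tests as complete-case sensitivity analyses.

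Table 1 already schedules all of these measures at screening, so no new data are needed, and recruitment and sample size do not change. Pooling does not itself require baseline adjustment or logs; they are included because the baseline is available at no extra cost and a log scale handles skewness without a rank test. The cost is a few lines of text, slightly more programming, and reporting of ratios for any hormone analysed on the log scale.

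### The primary comparison of AFC change does not use baseline AFC as a covariate; ANCOVA would probably be more precise at almost no cost, by an amount the documents do not let us fix

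*Protocol article*

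**What the plan says.** - **Endpoint** (Protocol article, Outcome measures): "The primary outcome is the change of AFC from baseline to week 12", with the difference between groups to be assessed.
- **Baseline data** (Study design): "Assessments will be conducted at baseline, week 12, and week 24". Table 1 lists AFC at screening, week 12 and week 24, so a baseline count is planned for every participant.
- **Test** (Statistical analysis): "Comparisons between groups will be analyzed using the independent" t test or a non-parametric test for continuous data. The non-parametric test is not named. No covariate or model appears anywhere in the article, and the section does not refer the choice to another document.
- **Missing data** (Statistical analysis): all randomized women are analysed, and "Missing data will be imputed using multiple imputation method".
- **Randomization** (Randomization and blinding): gender and birthday are entered into the central system. No balancing on baseline AFC is described.

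**The concern.** A change score subtracts the whole baseline value, which amounts to assuming that a woman who starts one follicle higher also ends one follicle higher. If the true slope is below 1, the subtraction over-corrects: women who start low tend to rise more. Two consequences follow.

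1. The treatment difference carries more variance than it needs to, because ANCOVA estimates the slope from the data instead of fixing it.
2. In the trial actually drawn, part of any chance difference in baseline AFC remains in the estimate as regression to the mean.

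A slope below 1 is likely here. AFC varies from count to count, and a low count is one of the routes into the trial. At stake is precision for the only primary endpoint. The rank-test branch has a further practical weakness: it gives no estimate and standard error that Rubin's rules can combine across imputed data sets, although the plan calls for multiple imputation.

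**Working it through.** **Inputs from Sample size.** The earlier study gave mean increases of "2.25 in acupuncture group and 0.30 in the wait list control". For the control arm, "we assumed an increase of 0.8 in AFC for sham acupuncture after 12-week treatment". The planned difference is therefore 2.25 − 0.80 = 1.45. The variability is given as "assuming a standard deviation of 2.22", read here as the SD of the change score. The recruited number is 60 per group, with 20% dropout allowed.

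**Assumed, not in the documents.** The correlation r between baseline and week-12 AFC, and the ratio k = week-12 SD / baseline SD.

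**Step 1: the plan's own figure.** The article states "A sample size of 50 participants per group will be needed to provide 90% power and a two-sided significance level of 5"%.

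n per group = 2 × (1.960 + 1.282)² × 2.22² / 1.45² = 2 × 10.507 × 4.928 / 2.1025 = 49.3, rounded up to 50.

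The exact non-central t calculation gives 51, with 89.9% power at 50. The stated size is reproduced and matches an unadjusted comparison of change.

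**Step 2: variance of ANCOVA relative to the change score.** With baseline SD s:

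- change-score variance: s²(1 + k² − 2rk)
- ANCOVA residual variance: s²k²(1 − r²)
- ratio: k²(1 − r²) / (1 + k² − 2rk), which reduces to (1 + r)/2 when k = 1
- slope of week-12 AFC on baseline AFC: rk; the ratio equals 1 when this slope is 1

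**Step 3: equal SDs (k = 1).** The change-score SD is held at 2.22. The calculation uses 48 per arm, which is 80% of 60. Unadjusted power there is 88.6% (non-central t).

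| r | Variance ratio | Effective SD | Power at 48 per arm |
|---|---|---|---|
| unadjusted | 1.00 | 2.22 | 88.6% |
| 0.3 | 0.65 | 1.79 | 97.5% |
| 0.5 | 0.75 | 1.92 | 95.5% |
| 0.7 | 0.85 | 2.05 | 93.0% |
| 0.9 | 0.95 | 2.16 | 90.1% |

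Effective SD is 2.22 × √ratio; at r = 0.5, for example, 2.22 × √0.75 = 1.92.

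**Step 4: larger SD at week 12 (k > 1).**

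| r | k | Slope rk | Variance ratio | Gain |
|---|---|---|---|---|
| 0.5 | 1.5 | 0.75 | 1.6875 / 1.75 = 0.964 | about 4% |
| 0.7 | 1.3 | 0.91 | 0.8619 / 0.87 = 0.991 | about 1% |
| 0.8 | 1.25 | 1.00 | 0.5625 / 0.5625 = 1 | nil |

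**Step 5: remainder of a chance imbalance (k = 1, 50 per arm).** The difference in change moves by −(1 − r) follicle per follicle of baseline difference. At r = 0.5 the implied AFC SD is 2.22 / √(2 × 0.5) = 2.22. A one-standard-error baseline imbalance is 2.22 × √(2/50) = 0.44, and it shifts the estimate by 0.5 × 0.44 = 0.22 follicle, against a planned 1.45. This is the variance loss of step 3 seen in a single trial, not an additional harm.

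**The case against.** Much of the opposing case stands.

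- **Baseline is not ignored.** The endpoint subtracts it. Only a regression-to-the-mean remainder is left, not the full imbalance.
- **The test is sound.** A reader might infer that the planned comparison is biased. Under 1:1 randomization it is not: the t test on change is unbiased and keeps its type I error, and its standard error already contains the variation in step 5.
- **The trial was sized for this test.** It reaches about 90% power at 50 per arm without a covariate. The 88.6% starting point reflects how dropout was allowed for (60 × 0.8 = 48), which is a separate matter.
- **The gain is uncertain.** Selection on low values can narrow the baseline SD, and AFC is expected to rise, so k above 1 is plausible. AFC is also only one of three alternative entry criteria, so strong selection on AFC is not established.
- **The open choice of test.** A reader might infer that the better of two p-values will be taken, with an inflated error rate. The article does not say that. Its wording can equally mean a choice by distribution, and the rule for that choice may lie in an analysis plan that is not shown.

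What does not fall is the core of the point. The article does state a covariate-free comparison, and baseline AFC is collected. Where the slope happens to be 1, ANCOVA loses only about one degree of freedom.

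**Conclusion.** The point holds as one of efficiency and of accuracy given the baseline imbalance actually drawn. It is not one of validity. With equal SDs and r from 0.3 to 0.9, ANCOVA would cut the variance by 35% down to 5% and lift power at 48 per arm from 88.6% to between 97.5% and 90.1%. With a larger week-12 SD the benefit may be a few percent or nothing. These figures rest on reading 2.22 as the SD of change and on assumed values of r and k. A slope below 1 is likely but not shown, so no single figure for the gain should be quoted. The change is worth making because the potential gain is material and the cost negligible.

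**What to change.** In Statistical analysis, name one primary analysis: ANCOVA of week-12 AFC on treatment group with baseline AFC as covariate, fitted in each imputed data set, with the estimate and standard error pooled by Rubin's rules. Use the same model, each with its own baseline, for the other continuous outcomes (FSH, LH, E2, AMH, SAS score, and AFC at week 24). Keep the unadjusted t test on change and a named rank test as sensitivity analyses. Age as a further covariate is optional.

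The cost is analysis wording and about one degree of freedom, with no new data or visits. Trial status reports data collection still in progress, so the change should be recorded before anyone sees outcomes by group.
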